### 2.8. Blinding

Due to security reasons, blinding of SOs and supporting coaches is not possible. Nevertheless, participants, members of the data safety monitoring board (DSMB), and data analysts (observer) are blinded until the end of the data analysis. The DSMB is independent from the sponsor.

### 2.9. Adherence of Therapists to the Protocol

Feedback to participants is automatized and otherwise manualized. Regular meetings between online coaches and an experienced supervisor will promote treatment consistency and regular supervision (one meeting per month).

### 2.10. Power and Sample Size Calculations

It is assumed that participants who take part in the experimental treatment show significantly lower values of self-reported dynamic risk factors inter-, and post-treatment controlling for baseline values as well as less officially recorded re-offenses in a 5-years follow-up, compared to the placebo condition. Within programs for individuals who have sexually offended, higher levels of motivation and better treatment engagement were associated with decreased attrition (128). The study design addresses this in a direct manner by providing an online motivation module at the beginning of the intervention. A rate of 50% of screened participants taking voluntarily part in the clinical trial is assumed. Based on the estimation of the ministry of Lower-Saxony and Baden-Wuerttemberg, it is expected to see 1,165 subjects eligible for participation during the recruitment period of which 50% (*N* = 582) are expected to participate in the study. Taking a dropout of 26.4% (128) into account, it is expected to see *N* = 428 subjects completing the web-based intervention or placebo intervention. With *N* = 214 subjects in both conditions (treatment and placebo) it is possible to detect small effects (*d* = 0.27) with a power of 80% at a significance level α = 5%. This effect size is in the expected range based on the above shown literature.

### 2.11. Statistical Analysis

All patients who discontinue from the study are identified and the extent of their participation in the study is reported. If discontinuation is due to clear evidence for recidivism or concrete preparation for or intention to recidivism (assessed by responsible SO or guiding therapist) the subject receives the maximal value for self-reported dynamic risk factors for the remaining measurements (assuming the worst case of a failed treatment). In all other cases of drop-out, the reason is recorded. The efficacy of the web-based intervention based on the first primary outcome measure (IoD) will be analyzed by means of Gaussian linear model for repeated measures (MMRM) with treatment group, time (six time-points; after each web-based intervention module (see Supplementary Table 1); treatment-by-time interaction, and the randomization strata as factors (offense type, type of CS, external treatment in addition to CSaU), and baseline measurements (at clearing up) of the outcome as co-variate. The error terms are assumed to follow a multivariate normal distribution with unstructured co-variance. Least squares mean changes from baseline are reported for the treatment groups with 95% confidence interval (CI) as well as the difference between the least squares treatment group means with 95% CI and *p*-value testing the null hypothesis of no treatment effect. The analysis is performed on the Intention-To-Treat (ITT) population comprising all patients who have completed at least one module. The second primary outcome measure (officially recorded re-offenses) will be analyzed by means of Cox proportional hazard model with treatment group, number of completed modules and the randomization strata (offense type, type of CS, external treatment in addition to CSaU, risk to re-offend at baseline). The effect of each module will additionally be analyzed using the Wilcoxon signed rank test for paired data comparing the pre- and post-module scores, adjusting the *p*-values using the Bonferroni-Holm's method to control the family-wise error rate. Economic analyses will be based on analytic modeling techniques. Data will be derived from the clinical trial (e.g., recidivism rates based on dynamic risk factors), the literature (e.g., tangible benefits), and experimental procedures (e.g., contingent valuation/revealed preference approaches to assess intangible benefits). Results of the analysis will be presented in terms of net benefit (NB) estimates and a benefit-cost ratios. The NB will be calculated as NB = tangible benefits + intangible benefits-intervention costs. The intervention will be considered cost-beneficial relative to the control condition if the NB is positive and the benefit-cost ratio exceeds 1.00 following standard economic decision rules. Since many cost parameters associated with ISAC and ICCSEM occur after the trial period, the cost-benefit of the intervention will be modeled for a 5-years period. Sensitivity analyses will be conducted to examine how the NB will be influenced by variations in model parameters.

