**Figure 1 F1:**
[figure not shown]
Overview of the web-based intervention. The web-based intervention (control as well as experimental) comprises six modules. Each module consists of four sessions (S). The participants can freely decide when they will work on the session. The next session becomes unlocked, when (1) 1 week has past since last session was completed and (2) all guided-tasks are successfully completed. Thus, participants are able to finish each module within 4 weeks (1 month).

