### 2.6. Procedure

The clinical trial starts on January 01, 2021 and ends on December 31, 2022. All potential participants are screened by their SO based on inclusion criteria and the SO hands out written information on the trial. If the potential participant is generally interested in participating, an individual meeting with an independent research assistant will take place at the supervision office. During this meeting, the research assistant provides detailed information about the goals and procedure of the trial, data security and advantages or disadvantages of taking part in the trial. If the potential participant is further interested to take part, he or she will receive an information letter, the informed consent, an intervention agreement, and a letter releasing the SO from the confidentiality obligation. In the intervention agreement, the participant agrees not to commit offenses during the participation and is informed that any violation will lead to exclusion. Furthermore, the research assistant performs the pre-intervention assessments (see Supplementary Table 1). If a potential participant does not want to take part in the trial, he or she will be asked for informed consent in filling out one questionnaire (QNP) and to allow to fill out the SSQ-CF checklist by the research assistant as well as the SSQ-SO by the SO. Further, the potential participant is asked for allowance to assess his or her officially registered re-offenses in a 5-years follow up in order to be able to control for a potential volunteer-effect. After obtaining the written informed consent, the intervention agreement, and the release from confidentiality, the participant is randomly allocated to the experimental or the control condition. The username as well as the initial password is delivered by post to the SO, who will give it to the participant. After the first log-in, the participant has to change the initial password due to security reasons. After changing the initial password, the participant has to go through an introduction, which explains the usage of the intervention website, before he or she can start with the first online module. The procedure for the placebo condition is the same as for the experimental condition, only the provided online contents differ. In both the placebo and the intervention condition, the provided content is divided into six online modules. Each module is further divided into four sessions. Each session has a duration of about 60 min and the participant is advised to finish one session per week. Consequently, the intervention as well as placebo consists of 24 sessions which can be completed in 24 weeks. The participant will be reminded by in-app messages or by the SO if he or she is late in finishing the next session. During both online conditions, data of primary outcome (IoD) is assessed at 7 measurement time-points. Except questionnaires which are filled out at clearing up all questionnaires are provided online within the web-based app. This ensures that the questionnaires are filled in at the predefined measurement time-points. Five years after the last patient out, re-offenses are assessed by officially documented re-offenses (see Supplementary Table 1 for an overview on measurement time-points).

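### Participants who stop the modules for reasons other than recidivism have no observed IoD afterwards, so the end-of-treatment comparison relies on a doubtful missing-at-random assumption for them

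*Protocol article*

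**What the plan says.** Section 2.11 analyses the IoD by MMRM with "time (six time-points; after each web-based intervention module" and "baseline measurements (at clearing up) of the outcome as co-variate". Section 2.6 states that "data of primary outcome (IoD) is assessed at 7 measurement time-points", which fits one baseline and six post-module measurements. The same section says that, apart from those completed at clearing up, "all questionnaires are provided online within the web-based app".

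The legend of Figure 1 describes the pacing: "The participants can freely decide when they will work on the session", and "The next session becomes unlocked, when (1) 1 week has past since last session was completed", provided that the guided tasks have also been completed.

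Section 2.11 treats stopping in two ways. If it is due to evidence of, preparation for or intention to recidivism, the participant receives the maximal score at all remaining measurements. Otherwise: "In all other cases of drop-out, the reason is recorded". The population labelled ITT is restricted to people with one or more finished modules. Section 2.10 plans for 582 participants and 428 completers: "Taking a dropout of 26.4% (128) into account".

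**The concern.** Collection of the outcome is tied to progress through the treatment. Someone who stops working on the modules never reaches the next IoD, so stopping treatment also ends observation of this primary outcome. An analysis labelled intention-to-treat should describe what happens to people offered the programme, including those who abandon it. Here their later status would be inferred from people who continued.

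That inference is sound only if, given baseline and earlier post-module scores, stopping is unrelated to the unseen scores. The protocol gives reasons to doubt this. Section 2.3.1 expects motivation to affect progress, success and dropout in this population, and section 2.10 links motivation and engagement to attrition. Section 2.3.1 also cites a review in which most people who abort a web-based intervention do so before treatment proper begins. Such people would have no post-baseline IoD and would be outside the analysis set.

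This cannot be left to an analysis plan. A later plan can choose a model or a sensitivity analysis, but it cannot recover values that were never collected.

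**Working it through.** **1. The plan's own figures (section 2.10).**
- Completers: 582 × (1 − 0.264) = 428.4, or 214 per arm, as stated.
- Size per arm for d = 0.27, two-sided 5%, 80% power: 2 × (1.960 + 0.842)² / 0.27² ≈ 215.3, so 216. With 214 per arm the power is 0.798. The sample-size statement reproduces.

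**2. Is there an IoD off treatment?**
- Section 2.6 counts 7 IoD time-points. Section 2.11 uses 6 post-module points and a baseline: 6 + 1 = 7.
- The abstract counts 8 follow-up points, which fits those 7 plus the five-year check of recorded re-offenses.
- The analysis population needs one finished module, which is what one would expect if no post-baseline IoD exists before then.
- The counts leave no visible room for an assessment after stopping. Supplementary Table 1 is not shown, so one cannot be fully excluded.

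**3. How many people?**
- 582 × 0.264 = 153.6, so about 154 are expected not to complete.
- This is an upper bound on those without an end value, because recidivism stoppers within it are assigned one. Their share is not given.

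**4. What could it do to the effect? (Illustration.)** Assume d = 0.27 among completers, 26.4% stopping in each arm, and stoppers keeping a fraction k of the effect. Then d over all randomised = 0.27 × (0.736 + 0.264 × k). Power is for IoD values from all 582 (291 per arm, SD 1).

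| k | d over all randomised | Power |
|---|---|---|
| 1 | 0.270 | 0.903 |
| 0.5 | 0.234 | 0.807 |
| 0 | 0.199 | 0.669 |

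**5. Departure from missing at random.** Suppose the model estimate is 0.27 and experimental-arm stoppers truly end δ SD worse than the model predicts. The difference over all randomised is 0.27 − 0.264 × δ:
- δ = 0.25: 0.204
- δ = 0.5: 0.138
- δ = 1.0: 0.006

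If stoppers in both arms are equally worse than predicted, the bias is δ times the difference in dropout. It is zero at equal dropout. At 31.4% against 21.4% with δ = 0.5 it is 0.10 × 0.5 = 0.05 SD. All values of k and δ, and the unequal dropout rates, are assumptions; the documents give none.

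**The case against.** Much of the case on the other side stands, and it limits the point.

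- **A completers-only analysis?** A reader might infer this, but the MMRM uses every post-module value from anyone with at least one finished module. Someone who stops after module 4 contributes four values.
- **Do all 154 lack an end value?** No. Section 2.11 assigns the maximal value to those who stop for recidivism-related reasons.
- **Is the effect overstated by 36%?** The ratio 0.27 / 0.199 = 1.36 invites this reading. It needs stoppers to keep none of the effect, even after several modules, and it treats the MMRM estimate as a completer effect. In section 2.10, d = 0.27 is the detectable difference, not a forecast result. The half-kept case gives 0.27 / 0.234 = 1.15.
- **Does pace differ between arms?** Time in the model is module number, so calendar times can spread. But section 2.6 gives both arms the same procedure, with reminders for those who are late, and section 2.4 gives the placebo the same mode, dose and support. Nothing states that pace differs by arm. Indexing by module also suits the stated aim of evaluating each module.
- **Are both primary outcomes affected?** No. Recorded re-offenses come from official records and do not depend on finishing modules.
- **Might the unseen supplement or an analysis plan settle it?** The supplement might list a further visit, though the stated counts do not suggest one. Missing-data sensitivity analyses may fairly be left to an analysis plan; collecting the values may not.

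None of this supplies an observed IoD for people who stop for other reasons.

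**Conclusion.** The point holds in a limited form. As described, the trial collects no IoD after the last finished module from participants who stop for reasons other than recidivism, and it leaves those who finish no module out of the population labelled ITT. For the first group, the end-of-treatment comparison depends on a missing-at-random assumption that the protocol's own reasoning makes doubtful. For the second, the comparison says nothing.

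Up to 26.4% of participants are concerned. The size of any bias is unknown. The illustrations run from no change to a fall from 0.27 to 0.199 if stoppers keep none of the effect, and further if experimental-arm stoppers do worse than predicted. The direction and amount cannot be fixed from the documents. The sample-size arithmetic is not in error. This is a cheap improvement to data collection, and it rests on reading the seven IoD time-points as baseline plus six modules.

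**What to change.** - Keep the post-module IoD for evaluating the modules.
- Add one IoD request at a fixed calendar time, at least at the planned end of the 24 weeks counted from randomisation. Send it through the existing app and reminders to every randomised participant who has not withdrawn consent, whatever their module progress.
- Use this value as the end-of-treatment time-point for everyone: finishers, slow continuers and stoppers. Module-timed and calendar-timed values then do not share a time-point, and nobody has to decide who is slow and who has stopped.
- Include randomised participants with no finished module in that analysis.
- Leave the stated maximal-value rule for recidivism stoppers as it is; their assigned value stands.

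The cost is one extra questionnaire per participant and a few more reminders, some of which fall to supervision officers. Some stoppers will not answer, so an assumption about missing data remains, but for fewer people. Slow continuers will be measured before they finish, so the result describes status 24 weeks after randomisation rather than after six modules.

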### 2.5. Outcome Measures

In a 5-years follow-up, officially recorded re-offenses are assessed and analyzed for both treatment arms. In order to control for inter-individual pre-treatment scores and risk-levels, the pre-treatment scores are included as co-variables in the model for the primary endpoints. Following the recommendations of Olver and Wong as well as Olver and Stockdale, treatment change is also measured by risk assessment tools and questionnaires (16, 17).

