
### 2.7. Randomization

The trial comprises two parallel groups (web-based intervention group and web-based placebo group). Subjects are randomly allocated to treatment using an allocation ratio of 1:1. The randomization lists are centrally generated using a computerized system (SecuTrial® www.secutrial.com, a for-profit organization) stratified by the offense type (§§176, 176a, 176b StGB vs. §184b StGB), type of CS (§§56, 57 StGB vs. §§68 ff StGB), treatment in addition to CSaU (external psycho-therapeutic and/or medical treatment vs. no treatment), and risk to re-offend at baseline [assessed with the modified Static-99 (43) for ICCSEM and the Static-99 (42) for ISAC]. At screening, each subject receives the next consecutive screening number. At randomization, each subject eligible for study participation receives the next consecutive randomization number according to his stratum from a block of randomization numbers (block size: 4).

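### The mixed model for the Index of Desistance lists three of the four randomisation strata and leaves out baseline risk to re-offend

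*Protocol article*

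**What the plan says.** Section 2.7 (Randomization) describes lists that are "stratified by the offense type (§§176, 176a, 176b StGB vs. §184b StGB), type of CS", then by "treatment in addition to CSaU (external psycho-therapeutic and/or medical treatment vs. no treatment". The fourth factor closes the list there: "and risk to re-offend at baseline [assessed with the modified Static-99 (43) for ICCSEM and the Static-99 (42) for ISAC". The number of risk categories used for this fourth factor is not stated.

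Section 2.11 (Statistical Analysis) specifies the MMRM for the IoD with treatment group, time and their interaction, "and the randomization strata as factors (offense type, type of CS, external treatment in addition to CSaU), and baseline measurements". The baseline term is the IoD itself: "baseline measurements (at clearing up) of the outcome as co-variate". Baseline risk to re-offend is absent.

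Later in the same paragraph the Cox model for officially recorded re-offenses has, besides treatment group and a count of finished modules, these terms: "and the randomization strata (offense type, type of CS, external treatment in addition to CSaU, risk to re-offend at baseline". Here all four factors appear.

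Section 2.5 (Outcome Measures) adds a general statement: "In order to control for inter-individual pre-treatment scores and risk-levels, the pre-treatment scores are included as co-variables in the model for the primary endpoints".

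**The concern.** The same phrase, the randomisation strata, has three members in one primary model and four in the other, within one paragraph. Whoever writes or programs the analysis cannot follow both the phrase and the three-item list, so two different primary models can be defended from the text.

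The statistical stake is the usual one for a stratified trial. Stratifying on a prognostic factor removes chance imbalance in that factor, so the treatment difference varies less than it would under simple randomisation. If the analysis model leaves the factor out, the variance that the factor explains stays in the residual. The standard error is then too large, the test runs below its nominal level, and some power is lost. The omitted factor could well be prognostic here, because section 2.5.1.2 describes the IoD as representing individual risk to re-offend.

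**Working it through.** **Count of strata**

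| Factor | Randomisation (2.7) | MMRM for IoD (2.11) | Cox model (2.11) |
|---|---|---|---|
| Offense type | yes | yes | yes |
| Type of community supervision | yes | yes | yes |
| Treatment in addition to usual supervision | yes | yes | yes |
| Baseline risk to re-offend | yes | **no** | yes |
| Total | 4 | 3 | 4 |

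**The plan's own sample size (section 2.10).** Inputs: d = 0.27 with SD 1, power 80%, alpha 5%, 214 completers per arm. Sidedness is not stated.
- Two-sided normal approximation: n per arm = 2 × (1.960 + 0.842)² / 0.27², which rounds up to 216. Power at 214 per arm is 79.8% and the detectable d is 0.271. This agrees with the stated figures for practical purposes. A one-sided test would need only 170 per arm, so two-sided is the reading that fits.
- Recruitment chain: 1,165 × 0.5 = 582.5, and 582 × (1 − 0.264) = 428.4, or 214 per arm. This reproduces.

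**Effect of the missing stratum.** Let R2 be the share of residual IoD variance that the stratum explains beyond baseline IoD and the other three factors. The document gives no value, so R2 is assumed over a range. The calculation treats the comparison as a single two-group contrast, as section 2.10 does, with standard error sqrt(2/214) when the residual SD is 1. With stratified balance, the true variance of the treatment difference is (1 − R2) times the variance that the model without the stratum estimates. Then:
- actual two-sided type I error, stratum omitted = 2 × [1 − Φ(1.96 / sqrt(1 − R2))]
- power, stratum omitted = Φ[(0.27 / sqrt(2/214) − 1.96) / sqrt(1 − R2)]
- power, stratum included = Φ[0.27 / (sqrt(1 − R2) × sqrt(2/214)) − 1.96]

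| Assumed R2 | Type I error, omitted | Power, omitted | Power, included | Gain (points) |
|---|---|---|---|---|
| 0 | 5.0% | 79.8% | 79.8% | 0 |
| 0.02 | 4.8% | 80.0% | 80.5% | 0.6 |
| 0.05 | 4.4% | 80.4% | 81.7% | 1.4 |
| 0.10 | 3.9% | 81.0% | 83.7% | 2.7 |
| 0.20 | 2.8% | 82.4% | 87.8% | 5.3 |

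Gains are taken from unrounded powers. The right comparator for the adjusted power is the omitted column, not a flat 80%: if the stratum explains variance, stratified allocation already makes the unadjusted difference more precise.

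**Sensitivity to dropout.** The type I error column assumes that balance survives into the analysed set. If 26.4% are lost at random, about 0.736 of the balancing benefit remains, and R2 in the first formula becomes 0.736 × R2, that is 0.0368, 0.0736 and 0.1472. The type I error is then about 4.6%, 4.2% and 3.4% for R2 = 0.05, 0.10 and 0.20. The direction is unchanged and the departure from 5% is smaller.

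**The case against.** The strongest reply is that this is a slip of wording. The sentence names the randomisation strata, the list in brackets falls one short, and the Cox list in the same paragraph shows what the phrase means. That may well be so, and nothing shows that the team has decided to exclude the factor. But the three-item list is what the published plan says, and it still has to be corrected.

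A second reply is that baseline IoD is already in the MMRM and measures much the same thing, so the Static-99 stratum may add little. This stands as a point about size. It is why R2 is defined beyond baseline IoD and why the low end of the range should be taken seriously. The document does not offer it as a reason for leaving the stratum out.

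A reader might also infer from section 2.5 that the Cox model is deficient because it has no pre-treatment IoD score. The document does not support that. Section 2.5 does not name the IoD, and re-offending has no pre-treatment score of its own. The Cox model already carries "offense type, type of CS, external treatment in addition to CSaU, risk to re-offend at baseline", so risk level is controlled. Section 2.5.1.2 says the three IoD instruments are still being evaluated, and nothing in the article shows that baseline IoD predicts re-offending beyond the Static-99. What remains is that section 2.5 does not say which baseline measure belongs to which model.

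**Conclusion.** The inconsistency is certain: four strata at randomisation, four in the Cox model, three in the MMRM, with no reason given. The consequence is modest. For assumed R2 between 0.05 and 0.20, leaving the stratum out costs about 1.4 to 5.3 points of power at d = 0.27 with 214 per arm, and the nominal 5% test runs at about 4.4% down to 2.8%. At R2 = 0.02 or less, the power cost is about half a point or below. These figures rest on an R2 that the document does not give, on stratified balance holding in the analysed set, and on a single two-group contrast standing in for the repeated-measures model.

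A reader might take the omission as a threat to the validity of the IoD result. It is not one: the error is conservative, it does not inflate type I error, no bias in the estimate is expected from it, and no sample size figure changes. The point is worth correcting because it leaves the content of a primary model open and the correction is free.

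**What to change.** In section 2.11, or in the analysis plan that implements it, add baseline risk to re-offend (the Static-99 or modified Static-99 stratum used at randomisation) to the MMRM factors, so that both primary models carry all four randomisation factors.

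At most, reword section 2.5 to say which baseline measure each primary model uses: baseline IoD for the MMRM, and the baseline risk stratum for the Cox model as it is now listed. No change to the Cox covariates is asked for.

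The cost is one line of text, or two with the rewording. The stratum must be known to randomise anyone, so no new data are needed, and the sample size stays as it is.

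### The IoD model imposes one baseline slope on all six visits; if that slope changes over the modules, the module-6 comparison loses some precision and, with arm-specific dropout, can be biased

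*Protocol article*

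**What the plan says.** Section 2.11 lists the terms of the IoD model: treatment group, time with six levels (one after each module), treatment-by-time, three of the randomization strata, and "baseline measurements (at clearing up) of the outcome as co-variate". The residual covariance is unstructured. Treatment-by-time is the only interaction named. Section 2.5 says no more on the form of the adjustment: "the pre-treatment scores are included as co-variables in the model for the primary endpoints".

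The reported result is a difference in least-squares group means with its confidence interval and p-value. No visit is attached to it. Section 2.5.1.2 defines the endpoint as a pre-post difference, which points to the last visit.

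On dropout, section 2.10 has "Taking a dropout of 26.4% (128) into account" and gives no split by arm or by baseline risk. Under section 2.11, participants who stop because of recidivism, or concrete preparation for it, receive the worst possible score at their remaining visits. Those visits are therefore not missing.

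**The concern.** A baseline term that is not crossed with time forces the same regression on baseline after module 1 (about 4 weeks) and after module 6 (24 weeks or later). If IoD scores drift away from their baseline values over the programme, the pooled slope is too steep at the last visit. Part of the baseline signal then stays in the residual, and precision falls.

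There is a second possible consequence. A likelihood-based repeated-measures model is used because it remains valid when dropout depends on observed data, including baseline. That property requires a correct mean model. If the slope is wrong at module 6 and those who leave differ in baseline IoD between arms, part of the baseline difference enters the treatment contrast. The target effect is small, so a modest shift is worth avoiding.

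**Working it through.** **The plan's own figure.** The inputs from section 2.10 are "50% (*N* = 582) are expected to participate in the study", 26.4% dropout, "With *N* = 214 subjects in both conditions (treatment and placebo", "it is possible to detect small effects (*d* = 0.27" and "with a power of 80% at a significance level α = 5". Section 2.7 gives 1:1 allocation, so 291 per arm.
- Completers: 582 × (1 − 0.264) = 428.4, or 214 per arm.
- Power: Φ(0.27 × √(214/2) − 1.96) = 0.798. Sidedness is not stated; one-sided power would be 0.875, so the figure is two-sided.

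The 80% reproduces. It is a plain two-group calculation with no baseline adjustment, so the form of the baseline term does not enter it.

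**Assumptions for the check.** The article gives neither the correlations of IoD with baseline nor how dropout depends on baseline. Five correlation patterns were tried, with SD 1 at every visit: constant 0.6; first-order autoregressive (AR) with parameter 0.9, 0.8 or 0.6; and a random intercept (0.4) plus AR 0.7.

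**Complete data.** Let r be the vector of baseline correlations at the six visits and S the residual covariance given baseline. The common-slope estimate tends to b = (1′S⁻¹r)/(1′S⁻¹1). The module-6 residual variance is then 1 − r₆² + (r₆ − b)², against 1 − r₆² with visit-specific slopes. For AR 0.8, r₆ = 0.262 and b = 0.667, so the variance is 0.931 + 0.405² = 1.095 against 0.931. The standard error (SE) ratio is √(1.095/0.931) = 1.084.

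**With dropout.** Both models were fitted by maximum likelihood with unstructured covariance to simulated data: 15,000 per arm, six runs, SEs scaled to 291 per arm, 26.4% monotone dropout unrelated to baseline, and a module-6 effect of 0.27 SD. Power is Φ(0.27/SE − 1.96).

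| Pattern | Correlation, module 1 → 6 | SE ratio, complete data | SE with dropout, common → visit-specific slope | SE ratio | Power at 0.27 |
|---|---|---|---|---|---|
| Constant 0.6 | 0.60 → 0.60 | 1.000 | 0.0749 → 0.0749 | 1.000 | 0.950 → 0.950 |
| AR 0.9 | 0.90 → 0.53 | 1.071 | 0.0828 → 0.0773 | 1.071 | 0.903 → 0.938 |
| AR 0.8 | 0.80 → 0.26 | 1.084 | 0.0975 → 0.0895 | 1.089 | 0.791 → 0.855 |
| AR 0.6 | 0.60 → 0.05 | 1.040 | 0.0992 → 0.0948 | 1.046 | 0.777 → 0.812 |
| Intercept + AR 0.7 | 0.82 → 0.47 | 1.040 | 0.0854 → 0.0819 | 1.043 | 0.885 → 0.909 |

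In variance terms, the excess with dropout is 9 to 19% under decay.

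**Bias at module 6.** The log-odds of dropout per SD of baseline was set separately in each arm. The table shows the common-slope estimate minus the visit-specific estimate on the same data, which removes shared simulation error. The standard error of this difference is 0.003 or less.

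| Pattern | 0.5 in one arm, 0 in the other | +0.5 and −0.5 |
|---|---|---|
| Constant 0.6 | 0.000 | 0.000 |
| AR 0.9 | 0.032 | 0.063 |
| AR 0.8 | 0.043 | 0.084 |
| AR 0.6 | 0.034 | 0.068 |
| Intercept + AR 0.7 | 0.027 | 0.055 |

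As a share of 0.27 SD under decay, this is 10 to 16% for one-arm dependence (0.027/0.27 to 0.043/0.27) and 20 to 31% for opposite dependence (0.055/0.27 to 0.084/0.27). With log-odds 0.5 in both arms, single large-sample runs differed by 0.004 SD or less between models. In the direction simulated, high-baseline participants left the experimental arm and the effect shrank. The reverse would inflate it.

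**If the contrast is averaged over visits.** Under decay the SE ratio falls to between 1.021 (0.0574/0.0562) and 1.045 (0.0601/0.0575). The net bias falls to between 0.012 (0.015 − 0.003) and 0.036 (0.039 − 0.003) SD.

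**The case against.** The strongest reply is that a baseline main effect with unstructured covariance is a recognised model, that the article condenses it into one sentence, and that an unseen analysis plan may add the interaction. But section 2.11 gives a term list and names treatment-by-time explicitly, so a single slope is its natural reading. The unstructured covariance recovers only part of the lost adjustment, through the earlier visits.

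Other parts of the reply stand:
- The article contains no correlation of IoD with baseline. The IoD sums three instruments, only one of which is an acute-risk tool, so a falling correlation is an assumption. Section 1.1 does say that potential to change depends on risk level, which makes a constant slope less likely but does not measure it.
- Arm-specific dropout is not documented. Section 2.10 links attrition to motivation, and only the experimental arm has the motivation module. Against that, section 2.4 matches support and attention across arms, section 2.8 blinds participants, and section 2.3.1 cites a review placing most abandonment before treatment begins.
- Recidivism-related exits receive the worst score, so part of the risk-related dropout produces no missing values.
- Section 2.11 names no visit for the contrast, and averaging over visits shrinks both consequences.
- A one-arm bias of at most 0.043 SD is under half a standard error.

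A reader might infer that the planned analysis is biased as it stands, or that the trial falls short of its stated power because of this term. The article supports neither. Bias needs a changing slope together with baseline dependence of dropout that differs by arm. The 80% was computed without baseline adjustment, and common-slope power in the decaying patterns is still 0.78 to 0.90.

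**Conclusion.** The point holds as a conditional improvement to the specification. The model as written imposes one baseline slope on six visits.
- **Slope changes over the modules:** the module-6 SE is about 4 to 8% larger than it need be with complete data, and 4 to 9% with the planned dropout. For a contrast averaged over visits the penalty is about 2 to 5%.
- **Constant correlation:** neither model has an advantage, and there is no bias.
- **Changing slope, and unimputed dropout that depends on baseline differently by arm:** the module-6 effect is off by about 0.03 to 0.04 SD for dependence in one arm and up to about 0.08 SD for opposite dependence, in either direction. With equal dependence in both arms the bias is negligible.

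The sizes rest on the assumed correlation patterns and dropout log-odds, not on data in the article. They do not show that the result will be biased, and they leave the stated power for d = 0.27 intact.

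**What to change.** In section 2.11, add a baseline IoD-by-time interaction to the repeated-measures model so that each visit has its own baseline slope. Report least-squares means at the overall baseline mean. Name the after-module-6 difference as the primary test, in line with the pre-post definition in section 2.5.1.2. Record the change before unblinding so that model choice cannot follow the data.

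The cost is five degrees of freedom (six slopes in place of one) with 428 expected completers, and no new data. Under a constant correlation the SE is 0.0749 with either model when dropout is unrelated to baseline. It rises only to 0.0755 for the interaction model under the opposite-dependence dropout tried.
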